## Abstract

**Background:**

The ‘Be the Best You Can Be’ (BtBYCB) program is a school-based intervention designed to foster positive physical, psychological, and social development via empowering young people to take ownership over their own personal development. The aim of this work is to determine the effectiveness of the BtBYCB program on (i) pupils’ well-being, self-perceptions, self-esteem, aspirations, and learning strategies; and (ii) changes in modifiable health-risk behaviors (i.e., physical activity, diet, smoking, and alcohol consumption).

**Methods/design:**

A two-arm cluster randomized controlled trial employing a wait-list control plus qualitative and mixed-method evaluations was used. Participants were school pupils from Years 7 and 8 (aged 11–13 years). Ten schools located in southwest England were randomly allocated to receive the BtBYCB intervention (n = 5 schools; 711 pupils) or a control condition (i.e., usual Personal, Social, and Health Education classes) (n = 5 schools; 622 pupils). Participants in the intervention condition received a program consisting of (i) a talk from an Olympian/Paralympian; (ii) 11 one-hour teacher-led PSHE classroom sessions in which pupils identified their aspirations, values, and interests and explored and acted on these via activities such as personal development planning, goal-setting, and peer-mentoring; and (iii) participated in a celebration event (e.g., second visit from Olympian/Paralympian and short individual presentations). Data were collected at baseline, post-intervention, and at 3-month follow-up.

Focus groups (pupils and teachers) and individual interviews (headteachers) were conducted in the 5 intervention schools to (i) gain an in-depth understanding of mechanisms of change; (ii) explore ways in which the participants’ motivation and engagement could be enhanced, and (iii) elicit user-feedback pertaining to how the program, content, and appeal could be improved.

A mixed-method approach was used to describe and explain the differing experiences of particular groupings within and across the intervention schools; i.e., those for whom the program was effective, those that experienced little, if any change, and those for whom the program led to an inverse effect.

**Discussion:**

The findings of this work will provide insight into the effectiveness of an innovative and child-centered program. The research will inform improvements to the BtBYCB program as well as other interventions targeting child/youth health and wellness.

**Trial registration:**

The trial is registered as Current Controlled Trials ISRCTN99443695.

## Background

The Be the Best You Can Be (BtBYCB) program was launched on the back of the awarding of the *Games of the Thirtieth Olympiad* to the city of London as part of the legacy aimed at inspiring the nation’s generation of children (i.e., going beyond the buildings and infrastructure provided by the games themselves). Developed and refined by a team of educational experts, education specialists/policy makers, and university scholars, the BtBYCB program was designed to foster positive physical, psychological, and social development by encouraging pupils to take ownership over their own personal development (i.e., becoming successful, creative and resourceful learners who are capable of living safe and healthy lives, and contribute positively to society). Such overarching aims and objectives directly align with key UK education, well-being and health policies and directives e.g., [1-4].

Following a staff-development day designed to enhance the facilitation skills of those who will be leading the program, the intervention commences with an inspirational ‘launch’ , facilitated by a talk from an Olympian, Paralympian, or other exceptional achiever. The launch session is intended to provide initial motivation to the pupils by helping them to understand what it feels like to be successful, the journey of personal growth involved, and the skills and dedication needed to achieve one’s dreams. The program continues with 11 one-hour teacher-led classroom sessions which are scheduled to occur within Personal, Social, and Health Education (PSHE) (although the topics can be linked across the curriculum in classes such as Physical Education). In these sessions, pupils are challenged to identify their aspirations, values, and interests and through activities such as *personal development planning*, *peer*-*mentoring*, and *self*-*coaching*, raise their awareness and develop the learning, self-management, self-reflection, and interpersonal skills necessary to support their identified ambitions, goals, and objectives. The program culminates with a final session (i.e., the ‘celebration’) in which the pupils are invited to deliver short group presentations to an audience consisting of fellow pupils, school staff, and invited guests (e.g., the guest speaker, parents, and members of the community). This presentation provides the pupil with an opportunity to reflect upon their personal achievements, share with others what the program meant to them, and reflect on the life-skills developed through the intervention. To facilitate the delivery of the program, each school has a BtBYCB team consisting of year tutors, teachers, PSHE staff, and a senior staff member.

With the intention of changing how pupils behave, view success, function, and develop skills for lifelong learning and health it is clear that an understanding of the motivation of pupils to engage and persist in the intervention is fundamental to the success of BtBYCB program. A general theory of human motivation that addresses the quality of motivation as well as the explicit conditions that promote optimal engagement, growth, health and development is *self*-*determination theory* (SDT; [5,6]). SDT is the product of a systematic and comprehensive program of inductive research spanning the past five decades, and proposes that the nature and focus of motivation that gives rise to action can vary greatly, and it is this variation in motivation quality that serves to predict the degree to which behavior is sustained, active, and effortful. SDT also provides explicit insight into how to foster improvements in (i) autonomous motivation and (ii) physical and psychological health. Broadly speaking, within SDT social conditions supportive of a person’s experience of three basic psychological needs for *autonomy*, *competence*, and *relatedness* are argued to foster the most volitional and high quality forms of motivation. This in turn promotes engagement with activities, including enhanced performance, persistence, and creativity [5,6]. In contrast, SDT proposes that the degree to which any of these three basic psychological needs are unsupported or thwarted within a social or cultural context, will relate to a measurable negative impact on an individuals’ quality of motivation and wellness (e.g., ill-being, passive engagement, and restricted development) [6].

The BtBYCB program is aligned with tenets embraced within SDT. To this end, SDT postulates that autonomous types of motivation result in positive consequences (e.g., optimal functioning, behavioral persistence, effortful engagement, eudaimonic and hedonic well-being), whereas controlling types of motivation lead to negative outcomes (e.g., school drop-out, elevated anxiety, and greater experiencing of ill-being). Considerable empirical work in education settings has shown autonomous forms of motivation to lead to a number of desirable outcomes such as academic persistence [7], higher quality learning [8], improved achievement [9], enhanced well-being [10], and greater levels of school engagement [11]. Parallel findings have been reported in a wide array of contexts including sport, business, health-care, and exercise settings [cf. 12,13].

An appealing feature of the SDT framework is that it provides explicit insight into how to foster increments in (i) autonomous motivation and (ii) physical and psychological well-being. Within SDT a number of malleable antecedents to the satisfaction of the psychological needs that can be readily incorporated into the proposed intervention are specified. For example, prior research demonstrates that to support the need for autonomy, social contexts (e.g., lessons) need to provide choice, promote initiation, and understanding, while minimizing the need to perform and act in a prescribed manner. When the need for autonomy is supported in this manner, autonomous enactment in activities, well-being, learning, behavioral persistence, and adaptive health-related consequences are all enhanced [12]. Such interpersonal social contexts are termed autonomy-supportive environments.

In addition to promoting autonomy-support, in this work we will also target the social conditions necessary to facilitate competence and relatedness. For example, to promote pupils’ perceptions of competence, many activities/tasks will have self-referenced (or task-involving) standards and indicators of improvement associated with them, and feedback will be provided in a similar self-referenced manner [13]. This will provide informational feedback to pupils helping them to learn what is involved in making further improvements and how to notice and acknowledge their progress rather than focusing on their performance relative to other pupils. To facilitate relatedness, certain tasks/activities (e.g., peer mentoring) will encourage small group activities to promote cooperation and reciprocal relationships [13,14].

A second line of research has shown goal content manipulations (i.e., framing “what” pupils may hope to obtain from taking part) presented in the form of text scripts to differentially predict pupils’ responses to desirable education outcomes such as persistence and performance [15,16]. Specifically, previous research has shown adaptive outcomes to be a function of promoting goals that are intrinsic in nature as opposed to those that are directed towards external indicators of worth. As such, in this work the foci will be towards “inwardly-focused” goals such as personal growth, affiliation, community contribution, and maintenance of physical health.

Finally, because certain activities underpinning personal growth, achieving personal excellence, and accruing health benefits are not always appealing (i.e., albeit desirable they can be mundane, repetitive, etc.), an understanding of how to support an individual’s motivation to partake in such activities represents an important aspect of this research application. To this end, a process proposed by SDT (i.e., internalization) provides valuable information as to how to promote adaptive engagement in less appealing activities. Specifically, to facilitate the internalization process, Deci and colleagues e.g., [17,18] have identified the following social conditions; (i) a meaningful rationale expressing why it is important to partake in the activity, (ii) the interpersonal context in which the behavior is performed to be supportive of the basic needs for autonomy, competence, and relatedness so as to facilitate autonomous regulation and integration, (iii) an acknowledgement of the pupils’ feelings and perspective about the activity, and (iv) the use of language that conveys choice rather than control. Again, these principles have been incorporated into the BtBYCB program.

### The present work: Research aims and hypotheses

#### Primary aim

The primary aim of this study is to provide an empirical assessment of the BtBYCB program via the use of a cluster randomized controlled trial (CRCT). Specifically, the following research aims and hypotheses will be addressed in this trial:

### Aims

• To statistically examine whether the BtBYCB intervention leads to increased levels of eudaimonic well-being, hedonic well-being, self-esteem, self-perceptions, and adaptive learning strategies.

• In view of the healthy lifestyle messages embedded in the program, statistically examine whether the BtBYCB intervention leads to desirable changes in reported modifiable health-risk behaviors (i.e., physical activity level, dietary intake, tobacco use, and alcohol consumption). Further, in a subsample we will test whether changes in objectively assessed physical activity levels occur as a function of participating in the program.

• Using (i) qualitative methods; and (ii) a mixed-methods approach, describe, analyze and explain the differing experiences of participants engaged in the BtBYCB program.

### Hypotheses

• Engagement in the BtBYCB intervention will lead to increases in markers of eudaimonic well-being, hedonic well-being, and self-esteem.

• Engagement in the BtBYCB intervention will lead to desirable improvements in reported modifiable health-risk behaviors (i.e., physical activity level, dietary intake, smoking, and alcohol consumption). Further, and in a subsample, we hypothesize that objectively assessed physical activity levels will increase as a function of participating in the program.

• It is hypothesized that pupil improvements on markers of health and well-being will be mediated by increases in their perceptions of an autonomy supportive teaching context, satisfaction of autonomy, competence, relatedness, and also by improved autonomous motivation scores.

#### Secondary aim/objective

In addition to the main CRCT, we will conduct two supplementary elements of work. Combined, these phases of work will provide rich information of the *lived experiences* of participants and provide greater insight and understanding of the program experiences and user needs.

The first segment of work involves focus groups (or individual interviews in the case of headteachers) with participants to explore how the underpinning principles within SDT can be/have been integrated into the BtBYCB program. This aspect of work will also build an in-depth understanding of the “active ingredients” of the program, will explore ways in which the participants’ need-satisfaction and motivation could be further enhanced, and look into ways in which the user-group (i.e., pupils, teachers and headteachers) think that the program and its content and appeal can be improved.

The second component of work pertains to a simultaneous mixed-method approach encompassing qualitative and quantitative methodologies. Specifically, this approach will go beyond the ‘elaboration’ stage used in the focus group work to a ‘complementary’ perspective cf. [19]. Indeed, the purpose of the mixed-methods element of this study is to gain an in-depth account of the differing experiences of the program for particular groupings. The quantitative data will be used to identify pupils in each of the five intervention schools with different experiences of the intervention (i.e., those for whom the program was most effective, those who gained little, if any, change from the program, and those for whom the program had inverse effects). Informed by the quantitative data (thus, a QUAN + qual notation), this approach will seek to gain an in-depth account of the program experiences of participants with contrasting profiles. This approach will provide an enriched account of the data in a synergetic fashion as quantitative methods are suited to specifying relationships and qualitative for explaining and understanding relationships [20].

## Methods/design

### Ethics

This research was approved by the University of Bath School for Health Research Ethics Approval Panel (ref. EP 08/09 45) and is registered with Current Controlled Trials (registration number: ISRCTN99443695).

### Design

A single center CRCT employing a wait-list control group, supplemented by focus groups and a mixed methods process evaluation. The unit of randomization was school. Individual pupils will be the unit of analyses, yet we will take into account the nesting effects of schools and classes.

### Participants and setting

Secondary school children aged between 11 and 13 years attending 10 schools in the southwest of England served as participants in this project. Following ethical approval, parental consent, and participant assent, 1333 pupils were recruited for the CRCT using a cluster sampling approach. Pupils were randomly assigned by their school to either (i) BtBYCB intervention (n = 711 pupils from 28 classes) or (ii) a control group receiving standard PSHE lessons (i.e., standard care; n = 622 pupils from 30 classes). For the secondary analyses, a randomly selected sample of pupils and teachers were selected from each of the five intervention schools (n = 5). For the mixed-methods element, participants in each of the five schools were stratified by outcomes using a tertile split so as to acquire a purposeful sample encompassing different pupil experiences of the BtBYCB intervention (8 participants per grouping in each of the 5 intervention schools).

### Inclusion/exclusion criteria

All Year 7 and 8 school pupils in classes at the participating schools were eligible to participate in the program and the associated research. An inability to be involved in the intervention sessions was the only exclusion criteria (i.e., based on the opinion of the participating school).

### Sampling and randomization

To reduce contamination effects and bias, school was used as the randomization unit in this work. Allocation to either the intervention or the control arms of the trial occurred after schools had been recruited. A block randomization (1:1 ratio) was performed by an independent agency (i.e., in this case a trained individual within the SouthWest Regional Development Agency) and the balance between the trial arms was based on the following strata: socioeconomic status, urban/rural, and small/large. In agreeing to partake in this work, the school’s senior management had to be willing to accept the randomization status of the school. Potential disappointment with being allocated to the control condition was offset by the use of a wait-list control.

### Sample size calculation

Using a sample size calculator software package [21], the 58 classes used in this work based on the average size of class (i.e., 25 pupils; [22]) permitted the detection, at the 5% significance and 90% power level, of a standard difference of 0.25 (i.e., .25 of a standard deviation can be detected with an intra-cluster correlation (ICC) of .05). In recognizing that some classes were smaller than the average 25 pupils, a more conservative estimate using the same criteria (5% significance with 90% power assuming an ICC of .05) showed that .27 of a standard deviation could be detected with 50 classes with 25 pupils in each cluster. The current sample size also accommodates analyses at school and classroom levels (i.e., pupils are nested within classes which are, in turn, nested within schools).

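### The power figures count 58 (or 50) classes as independent clusters although 10 schools were randomised, so 90% power at 0.25–0.27 SD is not supported

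*Protocol article*

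**What the plan says.** The Design section states: "The unit of randomization was school". Sampling and randomization repeats it: "school was used as the randomization unit in this work". The abstract gives the number of units: "Ten schools located in southwest England were randomly allocated to receive the BtBYCB intervention (n = 5 schools; 711 pupils", with five schools and 622 pupils in the control arm. Participants and setting gives the classes: "BtBYCB intervention (n = 711 pupils from 28 classes" and 622 pupils from 30 control classes, so 1333 pupils in 58 classes.

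The Sample size calculation section works from classes: "the 58 classes used in this work based on the average size of class (i.e., 25 pupils; [22]) permitted the detection". The difference in question is 0.25 SD, for 90% power, a 5% test and an ICC of 0.05. A second scenario, offered as conservative because some classes have fewer than 25 pupils, gives 0.27 SD with 50 classes of 25. The section closes: "The current sample size also accommodates analyses at school and classroom levels". It gives no school-level ICC and no calculation with schools as units.

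**The concern.** In a cluster trial, the precision of the treatment comparison is set by the randomised units. Here all classes in a school have the same allocation and share whatever makes that school's pupils alike. They also share delivery: teacher training is held separately for each school, and each school has its own program team. The effective number of independent units is therefore 10, with 8 degrees of freedom between schools, and not 58.

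At stake is how the trial's sensitivity is described. A reader who takes the paragraph at face value will believe that a true effect of 0.25 SD had a 90% chance of being detected.

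**Working it through.** **1. The article's own figures.** Inputs from the Sample size calculation section: 25 pupils per class, ICC 0.05, 90% power, 5% significance (two-sided assumed, since the side is not stated).

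- Design effect = 1 + (25 − 1) × 0.05 = 2.2.
- Detectable difference = (1.960 + 1.2816) × √(2 × 2.2 / n per arm).
- 58 classes: n = 58 × 25 / 2 = 725, so 3.2415 × √(4.4/725) = 0.2525 SD (stated 0.25).
- 50 classes: n = 50 × 25 / 2 = 625, so 3.2415 × √(4.4/625) = 0.272 SD (stated 0.27).

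One-sided 5% would give 0.228 and 0.246, and 80% power would give 0.218 and 0.235; neither pair matches. The arithmetic is right for its inputs. Those inputs make the class the independent cluster and include no school term.

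**2. School as the unit.** Inputs from the article: 5 schools per arm, 58/10 = 5.8 classes per school, 1333/58 = 23.0 pupils per class, same-class correlation 0.05. Assumed: the same-school correlation ρ, varied from 0 (no school correlation beyond class) to 0.05 (all of the correlation at school level). Equal school sizes are used for simplicity.

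- Variance of a school mean (in SD²): V = ρ + (0.05 − ρ)/5.8 + 0.95/(5.8 × 23.0).
- Standard error of the difference: SE = √(2V/5).
- Two-sided 5% test on 10 − 2 = 8 df: critical value 2.306. The noncentrality needed for 90% power is 3.712, so the detectable difference is 3.712 × SE.

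| School ICC ρ | V | SE | Detectable at 90% power | Power at 0.25 SD | Power at 0.27 SD |
|---|---|---|---|---|---|
| 0 | 0.0157 | 0.0794 | 0.295 | 79% | 85% |
| 0.01 | 0.0240 | 0.0980 | 0.364 | 61% | 68% |
| 0.02 | 0.0323 | 0.1137 | 0.422 | 49% | 55% |
| 0.05 | 0.0571 | 0.1512 | 0.561 | 31% | 35% |

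Example, ρ = 0.01: V = 0.01 + 0.0069 + 0.0071 = 0.0240; SE = √(0.4 × 0.0240) = 0.098; 3.712 × 0.098 = 0.364.

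**3. How much is due to the 8 df.** With normal quantiles instead, the detectable differences are 0.257, 0.32, 0.37 and 0.49 SD, and power at 0.25 SD is 88%, 72%, 60% and 38%. At ρ = 0 the shortfall therefore comes almost entirely from the few degrees of freedom. From ρ = 0.01 upward, the school term alone is enough to cause it.

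**4. Baseline adjustment.** Data Analyses plans ANCOVA on baseline. The article gives no baseline correlation; assume r = 0.6 at every level. SE is then multiplied by √(1 − 0.36) = 0.8.

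| School ICC ρ | Detectable at 90% power, adjusted | Power at 0.25 SD, adjusted |
|---|---|---|
| 0 | 0.236 | 93% |
| 0.01 | 0.291 | 80% |
| 0.02 | 0.338 | 67% |
| 0.05 | 0.449 | 44% |

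At ρ = 0.005 the adjusted detectable difference is 0.265 SD (86% power at 0.25 SD, 91% at 0.27 SD).

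**The case against.** Several points on the other side carry weight.

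- **The size depends on an ICC that the article does not give.** This stands. The result must be shown as a range that includes zero. The 0.56 SD end puts the whole 0.05 at school level, which is an extreme split.
- **The planned analysis adjusts for baseline.** This stands in part. Adjustment could restore the stated sensitivity if the school ICC is very small. But the sample size section does not invoke adjustment, and the rescue needs both an assumed baseline correlation and an assumed school ICC close to zero.
- **The analysis recognises school nesting.** Design and Data Analyses say so, and confidence intervals are planned. If school is fitted, the interval will show the real imprecision. A reader might infer that a null result is bound to be misread as excluding 0.25 SD; the planned intervals mean that this does not follow. The power statement itself remains unsupported.
- **The 50-class figure is conservative.** It allows for smaller classes only. It does nothing about schools.
- **The closing sentence may describe model structure.** That is a fair reading, since its parenthesis explains the nesting of pupils, classes and schools. It calls for qualification, not deletion.

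A reader might also infer that both figures rest on more pupils than were recruited. That is true only of the 0.25 SD figure (58 × 25 = 1450 against 1333). The 0.27 SD figure uses 50 × 25 = 1250, fewer than were recruited, so the criticism does not apply to it.

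**Conclusion.** The point holds as a wrong unit of clustering, not as an arithmetical slip. The 0.25 and 0.27 SD figures belong to a design with 58 or 50 independently allocated classes, and this trial allocated 10 schools.

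Without baseline adjustment, the difference detectable with 90% power is about 0.30 to 0.56 SD for school ICCs from 0 to 0.05, and power at 0.25 SD runs from about 79% down to 31%. This rests on the article's same-class correlation of 0.05, 1333 pupils, equal school sizes, a two-sided 5% test on 8 df and an assumed school ICC. On that basis power is below 90% at both stated differences across the whole range. With an assumed baseline correlation of 0.6 the range is about 0.24 to 0.45 SD, and the stated sensitivity is reached only at a near-zero school ICC.

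The documents do not support going further and saying that the planned analysis ignores schools, or that the stated sensitivity is out of reach under every assumption.

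**What to change.** Rewrite the Sample size calculation paragraph:

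- Take school as the randomised cluster: 10 schools, 5 per arm, class nested in school, 8 df, N = 1333.
- Give the detectable difference at 90% power over school ICC 0 to 0.05, both unadjusted and baseline-adjusted, and label the school ICC and the baseline correlation as assumptions.
- Put that range in place of the claim of 0.25/0.27 SD at 90% power.
- Qualify the closing sentence so that it describes the levels in the model and does not suggest adequate power at school level.

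The cost is one paragraph and a less favourable stated sensitivity. No extra schools are needed, and no planned estimate or test changes.
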